## Abstract

Chronic pain is common and debilitating in cancer survivors. Tibetan herbal pain-relieving plaster is used as an external analgesic to treat musculoskeletal pain in China; however, its safety and efficacy have not been evaluated via clinical trials in cancer survivors. We designed this Phase II randomized, double-blind, placebo-controlled trial (ClinicalTrials.gov Identifier: NCT04916249) to assess the efficacy and safety of the pain-relieving plaster for temporary pain relief among cancer survivors with chronic musculoskeletal pain. Under ethical approval from the Institutional Review Board at the Memorial Sloan Kettering Cancer Center, we will enroll eligible cancer survivors who have a clinical diagnosis of moderate to severe chronic musculoskeletal pain in this study. We use a central randomization system to allocate the eligible participants to either the treatment or the control group in a 1:1 ratio, with stratification by baseline opioid use. We will instruct the participants to apply the herbal patch (Tibetree Pain-Relieving Plaster, Tibet Cheezheng Tibetan Medicine Co. Ltd., Tibet, China) or placebo patch daily at the focal area with worst pain for 14 consecutive days. Study physician, participant, outcome assessor, and biostatistician are blinded to the group allocation. The primary outcome is pain severity measured by the Brief Pain Inventory on Days 2–7. Secondary outcomes include changes in insomnia, anxiety, depression, fatigue, pressure pain threshold, pain medication use, and global impression of change. We will also monitor the adverse events throughout the study period. Statistical analysis will follow the intention-to-treat principle and linear mixed modeling will be used. With rigorous design and implementation, this randomized, placebo-controlled trial will provide the initial evidence on the efficacy and safety of the pain-relieving plaster for pain relief among cancer survivors with chronic musculoskeletal pain.

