In the Asia-Pacific region and the U.S., Tibetree Pain-Relieving Plaster (PRP) (National Drug Code: 66506-186)–a patented herbal medicine made with 1% Camphor (Cinnamomum camphora (L.) Nees and Eberm) and other herbal species (Table 1)–is used as an over-the-counter external analgesic for the relief of various musculoskeletal pains (Wen et al., 2019). In an NCI-designated cancer center, patients who used PRP reported improvements in pain that has not been satisfactorily addressed by oral analgesics (Liou et al., 2021). Herbs in PRP have antinociceptive and anti-inflammation effects, through decreasing C-fiber afferent spontaneous firing and reducing the release of inflammatory cytokines (Peng et al., 2011; Duan et al., 2013). Our systematic review revealed that PRP was associated with clinical improvements in pain and joint function for musculoskeletal pain among non-cancer populations (Chen et al., 2020; Yang et al., 2021a). Nonetheless, no placebo-controlled randomized trial has been conducted. Additionally, its effect remains unknown in cancer survivors. Therefore, we designed this phase II study to 1) evaluate the preliminary efficacy and safety of two-week PRP treatment versus placebo for immediate pain relief among cancer survivors with chronic musculoskeletal pain, 2) obtain estimates of change in comorbid insomnia, anxiety, depression, and fatigue, quality of life, global impressions of change, and pain medication usage, 3) explore potential clinical and/or biological traits in association with analgesic response to treatment, such as patient expectancy, pressure pain threshold (Diatchenko et al., 2013).

**TABLE 1 T1:** Composition of the Tibetan herbal pain-relieving plaster.

CHN Pinyin	ENG Name	CHN Name	Scientific Name of Plant^b^	Family Name	Medicinal Parts
*Zhangnao*	*Camphor* ^a^	樟脑	*Cinnamomum camphora* (L.) Nees and Eberm	*Lauraceae* Juss	Bark
*Duyiwei*	*Lamiophlomis Herba* ^a^	独一味	*Phlomis rotata* Benth. ex Hook.f	*Lamiaceae* Martinov	Whole herb
*Jianghuang*	*Curcumae Longae Rhizoma* ^a^	姜黄	*Curcuma longa* L	*Zingiberaceae* Martinov	Rhizome

a According to the Pharmacopeia of China 2015.

b Tropicos v3.3.2 (Tropicos.org. Missouri Botanical Garden. 30 March 2022 <https://tropicos.org>).

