### 2.4 Blinding

The CRCs, patients, clinicians, PI, co-investigators, biostatisticians will be blinded to the group allocation. The MSK research pharmacy will maintain the randomization and distribution list of the PRP and placebo medications. Pharmacist who dispenses the patches will have no contact with patients and a study clinician will pick up the plasters from the pharmacy and distribute them to patients on their Day 1 visit.

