#### 2.6.2 Secondary Outcomes

• Pain severity and interference measured by the BPI at day 14.• Patients’ Global Impression of Change (PGIC) is a one item survey that will be used to define a clinically important change in pain from the patient’s perspective (Sloan et al., 2002). Patients will be asked “Compared to when the study began, how would you describe your pain now? I am: very much worse, much worse, a little worse, the same, a little improved, much improved, very much improved.” The PGIC can be used as an anchor to derive anchor-based minimally important differences (MIDs) for pain measures like the BPI.• Brief Fatigue Inventory (BFI) will be used to determine the effect of treatments on fatigue. This 9-item instrument was designed to assess one construct of fatigue severity in cancer and non-cancer populations. Three items ask patients to rate the severity of their fatigue at its “worst,” “usual,” and “now” during normal waking hours, with 0 being “no fatigue” and 10 being “fatigue as bad as you can imagine.” Six items assess the amount that fatigue has interfered with different aspects of the patient’s life during the past 24 h. The interference items are measured on a 0–10 scale, with 0 being “does not interfere” and 10 being “completely interferes” (Sloan et al., 2002). A composite fatigue severity score can be found by averaging the nine item scores. The score of the scale was found to be reliable and valid in multiple languages and diverse populations (Sloan et al., 2002; Lin et al., 2006).• Insomnia Severity Index (ISI) will be used to measure subjective insomnia severity. The ISI has seven items rated on a 5-point Likert response scale (e.g., 0 = no problem; 4 = very severe problem), yielding a total score ranging from 0 to 28 with higher scores representing more severe insomnia symptoms. The usual recall period is the “last month”; however, we will use a modified recall period of “the past week” to match our assessment schedule. The ISI authors suggest the following guidelines for interpreting the ISI total score: < 8, no clinically significant insomnia; 8-14, subthreshold insomnia; 15-21, clinical insomnia (moderate severity); >21, clinical insomnia (severe).(Bastien et al., 2001). The ISI has demonstrated internal consistency, reliability, construct validity, specificity and sensitivity in a representative sample of 1670 cancer patients.(Savard et al., 2005). The ISI has established minimally important change values to ensure that the change is not only statistically, but also clinically, meaningful to patients.(Morin et al., 2011). A reduction of eight points has been deemed to be clinically significant improvement. (Morin et al., 2011).• Hospital Anxiety and Depression Scale (HADS) will be used to explore the effect of treatments on psychological distress. HADS is a 14-item scale with seven items measuring depression and seven items measuring anxiety. Each item is answered by the patient on a four-point (0–3) response category so possible scores range from 0-21 for anxiety and depression, with higher scores indicating higher symptomatology. Established cutoffs are: 0–7 not significant; 8–10 subclinical; and 11–21 clinically significant depression/anxiety.(Zigmond and Snaith 1983). Factor analysis showed two distinct but correlated factors of anxiety and depression.(Moorey et al., 1991). The scale scores have been shown to be both reliable and valid.(Smith et al., 2002).• Patient Reported Outcomes Measurement Information System (PROMIS®) Scale v1.2 - Global Health is a brief instrument composed of 10 items that demonstrates adequate reliability and validity (Hays et al., 2009; Revicki et al., 2009) as a measure of health related QOL in general and clinical populations.(Rothrock et al., 2010; Barile et al., 2013). Patients are asked to respond to questions 1-8 and 10 on a scale of 1–5. Question nine is on a 0–10 scale (average pain rating). The measure yields two scores, Physical Health and Mental Health, that will be used as secondary outcomes to evaluate the effect of Tibetree PRP on QOL.(Hays et al., 2009). These scores will be calculated using item-level calibrations based on item response theory (IRT) scaling and then transformed to T-Scores, which are standardized such that 50 represents the mean for the US general population, and the standard deviation around that mean is 10 points.(Hays et al., 2009). Higher scores indicate better Physical and Mental Health.• MAO Expectancy of Treatment Effects (METE) has four items originally developed as the Acupuncture Expectancy Scale (AES) by Mao et al.(Mao et al., 2007) It has demonstrated reliability (Cronbach’s α of 0.82) and validity and is positively correlated with patient self-reported efficacy and satisfaction.(Mao et al., 2007). The score ranges from 4 to 20, with higher scores indicating greater expectancy.• Mao Expectancy of Side Effects of Treatment (MESET) measures the expectations of side effects and therapeutic effects of the study intervention.(Mao et al., 2014). The score ranges from 4 to 20, with higher scores indicating greater expectancy for side effects. We will use the METE and MESET to explore whether expectancy predicts treatment outcomes and may impact the observed differences between groups.• Pressure Pain Threshold: This is a study measure that a study investigator will administer. Pressure algometry is a reliable measure of pressure pain threshold. Two types of algometers will be used in this trial:(1) the FPX Wagner algometer: We will use a digital pressure algometer, FPX (Wagner instrument, Greenwich, United States), to apply pressure at the site of pain (the tender points of tissue where the patient experiences the worst pain) and two pain-neutral areas (thumbnail bed and trapezius) to derive the pressure pain threshold (the first pressure that is perceived as painful) shown to be predictive of analgesic effects (Harte et al., 2013a; Wasserman et al., 2015). The clinical researcher will apply pressure at a 0.5 kgf/cm^2^/sec increment at the tissue located at or surrounding the tested site with the tip of the algometer. The test will be terminated when participants reach their pain threshold or a pressure of 10 kgf/cm^2^. The test will be repeated three times per site, and we will take the mean threshold for analysis, measured as kgf/cm^2^. The test will be conducted three times during the study: before patch application at baseline; 45 min after patch application at baseline and at the primary endpoint (Day 7).(2) the MAST system: We will use the MAST System (Arbor Medical Innovations, Ann Arbor, MI) (Harte et al., 2013b; Schrepf et al., 2015; Wasserman et al., 2015; Treister et al., 2018; Harte et al., 2019) to apply computer-controlled pressure at the thumbnail bed to derive the PPT as well as suprathreshold measures of pain sensitivity (e.g., pain tolerance) shown to be predictive of analgesic effects.(Harte et al., 2013a; Wasserman et al., 2015). The system delivers ascending and random patterns of discrete pressures (5 s duration; 4 kgf/cm^2^/s ramp rate) at 20 s intervals, beginning at 0.25 kgf/cm^2^ and increasing in 0.25–0.50 kgf/cm^2^ steps. Pain intensity will be rated after each stimulus on a 0–100 Numerical Rating Scale. The test will be terminated when participants reach their tolerance or 10 kgf/cm^2^. PPT test with the MAST system will be conducted once before patch application at baseline only. The validity of testing pressure pain threshold with the MAST system has been demonstrated extensively (Petzke et al., 2001; Gracely et al., 2002; Giesecke et al., 2003; Petzke et al., 2003; Petzke et al., 2005; Harris et al., 2006; Geisser et al., 2008; Harris et al., 2008; Harris et al., 2009; As-Sanie et al., 2013; Henry et al., 2014; Clauw 2015). We will use this measure to explore whether pressure pain threshold predicts treatment outcomes and impacts the observed differences between groups. We will also incorporate the pressure pain threshold into the clinical outcomes to provide more objective, less biased quantification of pain and more accurate assessment of the analgesic effect of the herbal patches.• Study Allocation Belief: This is a patient-reported outcome that asks patient to guess which treatment they have received during the study to assess the adequacy of blinding.• Pain Medication Diary: Name of pain medication, the dosage/strength, number of days patients took the medication and how many pills were taken were collected in the Pain Medication Diary. A pain medication usage score was calculated according to the method developed by Robinson-Papp et al. (Robinson-Papp et al., 2015).• Adverse events: We will document all related adverse events and report any related serious adverse event promptly to IRB.

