#### 2.8.1 Populations for Analyses

All randomized patients will have a baseline pain assessment, and those with at least one post-baseline BPI assessment on or before Day 7 will be included in the analysis of the primary objective using the modified ITT principle (i.e. participants will be analyzed according to the treatment group to which they will be randomly allocated regardless of treatment adherence status). Secondary outcome such as insomnia, anxiety, depression, fatigue, and quality of life are measured at baseline, Day 7, and Day 14. The analysis population for these endpoints will include patients who complete the baseline and one or both of the Day 7 and Day 14 assessments. Pressure pain threshold is measured at baseline before patch application, baseline 45 min after patch application and Day 7. The analysis population for this endpoint will include patients who complete the test at baseline before patch application and one or both of the other two timepoints. Additionally, all patients who apply at least 1 of the study plasters will be included in the analysis of safety.

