#### 2.8.3 Analysis Plan for Secondary Objectives

The number and percent of adverse events within each treatment arm will be reported by grade. We will compare changes between the arms in insomnia, anxiety, depression, fatigue, quality of life, and pain medication usage scores using linear regressions predicting these endpoint scores at Day 7 and Day 14 (separate models) as a function of treatment arm, controlling for baseline score and randomization strata. This is equivalent to an ANCOVA model. The same analysis will be performed for PPT for the baseline (45 min after patch application) and Day 7 assessments, controlling for the pre-patch baseline assessment. We will summarize responses to the PGIC at days 2, 7, and 14 using frequencies and percentages by arm, and test for differences between arms using chi-square tests. To obtain estimates of the correlation of treatment expectancy and treatment response, we will fit a LMM similar to that specified for the primary objective, but with the addition of METE score and the interaction between treatment arm and METE score. To evaluate whether PPT predicts treatment response, we will fit a LMM similar to that specified for the primary objective, but with the addition of baseline (pre-patch) PPT score and the interaction between treatment arm and PPT baseline (pre-patch) score. Pain response variations in associated with other variables, such as sex, race/ethnicity, or age, may be addressed in post hoc analyses.

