Pain and comorbid symptoms like insomnia and depression may share common neurobiological pathways (Finan and Smith 2013). Recent studies indicate that nonpharmacologic pain interventions like cognitive behavioral therapy for insomnia or acupuncture may improve both pain and comorbid symptoms via regulating these shared biological pathways (Yang et al., 2021b). The present study will also provide insights into the clinical effect of PRP on pain comorbid symptoms that are prevalent in cancer survivors, including emotional distress, fatigue, and insomnia (Pachman et al., 2012). Furthermore, previous studies have linked patient psychosocial characteristics (such as patient expectancy (Smeets et al., 2008)) and pain phenotype (such as pain threshold (Zucker et al., 2017)), to the variations in response to pharmacologic or nonpharmacologic treatments. We will further explore potential phenotypic biomarkers that may predict pain response to treatment.

Although PRP may not impose serious side effects when used as a topical analgesic among chronic pain populations, moderate skin irritations were reported in observational studies, including skin dryness, redness, and blistering in the area where patch is applied (Chen et al., 2020; Yang et al., 2021a). As pharmacosurveillance of potential herb-drug interactions is critical to safety integrative care, this study will also enable us to gain important insights into the safety profile of PRP in cancer survivors. As many survivors are interested in herbal products, this study can potentially guide the establishment of a safe and novel pain control approaches to improve the quality of life for cancer patients.

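### Section 2.6.2 limits adverse event documentation to events judged related, so events judged unrelated cannot be compared with placebo or recovered later

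*Protocol article*

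**What the plan says.** The adverse event entry in section 2.6.2 reads: "We will document all related adverse events and report any related serious adverse event promptly to IRB". The word 'related' governs both halves of the sentence: what is documented, and which serious events are reported promptly.

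Other parts of the article are wider:

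- The Abstract sets no relatedness limit: "We will also monitor the adverse events throughout the study period".
- The Introduction makes safety part of the first aim, in comparison with placebo: "evaluate the preliminary efficacy and safety of two-week PRP treatment versus placebo for immediate pain relief among cancer survivors".
- Section 2.8.3 gives the summary, also without the word 'related': "The number and percent of adverse events within each treatment arm will be reported by grade". It does not say what the percent is a percent of.
- Section 2.8.1 defines the safety population by patient: "all patients who apply at least 1 of the study plasters will be included in the analysis of safety".
- Section 2.4 covers the people who would judge relatedness: "The CRCs, patients, clinicians, PI, co-investigators, biostatisticians will be blinded to the group allocation".
- The Discussion expects the trial to inform the safety profile in survivors ("this study will also enable us to gain important insights into the safety profile of PRP in cancer survivors") and lists the reactions known so far: "moderate skin irritations were reported in observational studies, including skin dryness, redness, and blistering in the area where patch is applied".

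**The concern.** A randomized placebo arm allows attribution by comparing arms: if an event is more frequent on active patch than on placebo, that excess is the evidence, whatever anyone thought of the single case. A rule that admits only events already judged related puts individual opinion ahead of that comparison.

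Reactions under the patch will probably pass the filter. The events at risk are those away from the patch site or not yet described. Section 2.2.1 admits survivors on continued hormone treatment or maintenance targeted therapy and lets patients keep their current pain regimen, so such events will often have another plausible explanation. Section 2.5.2 itself allows for side effects that are not yet known.

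This is stated text about data collection, not a detail left to a fuller document. An analysis plan can change how recorded events are tabulated. It cannot add events that were never written down.

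**Working it through.** The plan gives no adverse event rate, between-arm safety test or safety power, so there is no safety figure to reproduce. The check is a comparison of the texts, followed by illustrations on assumed values.

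**1. Texts side by side.** Section 2.6.2 documents related events. The Abstract monitors adverse events and section 2.8.3 reports adverse events, neither with that limit. The first aim is a comparison with placebo. If section 2.6.2 governs, the section 2.8.3 table can hold only related events and does not say so. If the Abstract governs, section 2.6.2 is worded too narrowly. The two need reconciling.

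**2. What a zero count would mean.** Inputs: 66 patients and 1:1 allocation (sections 2.1 and 2.3), so up to 66/2 = 33 per arm in the safety population.

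- With full capture, no case in 33 patients gives a one-sided 95% upper bound of 1 − 0.05^(1/33) = 0.0868, or 8.7%. This part reflects sample size alone.
- If only a share f of true cases is judged related and recorded, the bound applies to f × risk, so the bound on the true risk is 0.0868/f.

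| f (assumed) | Upper bound on true risk |
|---|---|
| 1.00 | 8.7% |
| 0.75 | 0.0868/0.75 = 11.6% |
| 0.50 | 0.0868/0.50 = 17.4% |
| 0.25 | 0.0868/0.25 = 34.7% |

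**3. What happens to a difference between arms.** Assume all-cause patient rates of 40% and 20%, 33 per arm, and the same f in both arms, as blinding would imply. The visible difference is f × (40 − 20) points. Power (normal approximation, two-sided 0.05) is only a yardstick, since no test is planned.

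| f (assumed) | Visible rates | Difference | Power |
|---|---|---|---|
| 1.00 | 40% vs 20% | 20 points | 0.42 |
| 0.75 | 30% vs 15% | 15 points | 0.31 |
| 0.50 | 20% vs 10% | 10 points | 0.20 |
| 0.25 | 10% vs 5% | 5 points | 0.12 |

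The difference shrinks but keeps its direction. In practice f would vary by type of event: near 1 for patch-site reactions, lower for systemic events.

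**4. The unstated base of the percent.** Suppose 2 of 33 patients have one grade 2 event each. As patients, that is 2/33 = 6.1%. As a share of events, it is 2/32 = 6.3% if the arm also has 30 grade 1 events, but 2/4 = 50% if it has only 2. The base therefore needs stating.

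**The case against.** The case for leaving the plan alone has four parts.

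- **Blinding.** Coordinators, clinicians and investigators do not know the arm, so the relatedness judgement should work alike in both. This stands. A reader might infer that the safety comparison is biased toward one arm, but the documents do not support that. It would need blinding to fail, for example through smell or skin reactions, and nothing in the article shows that it does. Blinding does not, however, recover events that were not recorded.
- **The expected harms would be kept.** Skin reactions under the patch are the events most likely to be called related, and a blinded assessor can also call an unexpected event related. This stands too, and it limits the loss. It does not remove the loss for events with another plausible cause.
- **The wording may be loose.** The Abstract and section 2.8.3 are unrestricted, and section 4 places the trial under a Data and Safety Monitoring Committee. Practice may be wider than the sentence in section 2.6.2. That is a reason to correct the sentence, and it lowers confidence that events are in fact being lost.
- **Table details belong in an analysis plan.** This is fair for the percent. A reader might infer from section 2.8.3 that the percentages are of events and that the safety analysis lacks a valid denominator. The text does not establish that: section 2.8.1 supplies a patient-based population, and section 2.8.3 may simply mean patients with an event. Only a clarification is warranted.

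A reader might also take the Discussion to make detection of herb-drug interactions a study aim. It calls such surveillance critical and promises insight into safety, but sets no such objective.

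**Conclusion.** The point holds in a limited form. As written, section 2.6.2 makes judged relatedness the condition for documentation. This conflicts with the unrestricted monitoring statement in the Abstract and serves the safety-versus-placebo aim poorly. The consequence is lost and diluted information, mainly on unanticipated or systemic events, and it cannot be repaired at the analysis stage. The primary efficacy conclusion is unaffected.

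The size is unknown, because the documents give neither event rates nor the share of events judged related. The figures in the working depend on the assumed shares (25% to 100%), on equal shares in both arms and, for the difference, on assumed rates of 40% and 20%. They show how the loss would act and are not estimates for this trial. Confidence is moderate, since the full protocol may word the collection rule more widely.

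**What to change.** Reconcile section 2.6.2 with the Abstract and section 2.8.3:

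- Record every adverse event from first patch to Day 14, whatever its judged relationship, with grade and attribution as separate fields.
- Report all-cause and related events side by side for each arm.
- As a clarification in section 2.8.3, state the percent as patients with at least one event, by worst grade, over the safety population of section 2.8.1. Event counts can be added as a supplement.

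The point concerns what is documented. It does not ask for a change to which serious events are reported promptly to the IRB.

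The cost is a small wording and form change and slightly more data entry for 66 patients over 14 days. Patients already receive a daily REDCap form (section 2.5.2). Section 4 says that enrolment is under way, so the change should be made soon and its date reported: events left unrecorded before it stay missing.
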